While the clinical role of CRRT has become well-established, there exists tremendous variability in how CRRT is prescribed and delivered [12–14]. The KDIGO AKI guidelines provide some recommendations, stating that the target delivered CRRT effluent dose should be 20–25 mL/kg/h, and also suggesting that regional citrate should be the first-line form of anticoagulation [8]. However, specific recommendations are lacking for a number of other important areas, such as CRRT modality, details of anticoagulation protocols, electrolyte supplementation practices, or approach to fluid balance. This reflects the lack of strong evidence upon which to base guidelines, as most studies examining CRRT practices have been relatively small and/or single-center. In addition, despite the high-risk nature of the patient population, very few studies have examined quality metrics and/or patient safety related to CRRT practices [15].

Here we describe the protocol for a prospective observational study focused on CRRT practices in critically ill adult patients across a network of medical centers in North America (CRRTnet). Our goal is to develop a large repository of data regarding CRRT practices and outcomes, allowing characterization of similarities and differences in standard CRRT practices across medical centers. The natural variability in practices between (and even within) centers will provide the ability to compare outcomes between different practice patterns and generate important preliminary data to inform future interventional trials. In addition, a long-term goal for CRRTnet is to establish benchmarks for best CRRT practice for centers both within and outside the study.

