### Data collection

Data will be collected encompassing a wide range of variables examining patient characteristics at enrollment, describing daily ICU course, capturing details of CRRT, and describing patient outcomes. Each participating medical center utilizes an electronic medical record which will serve as the primary source for data extraction.

The initial intake form includes demographic variables, and baseline patient characteristics at the time of CRRT initiation (Table 1). Fluid balance (in liters) between the time of ICU admission and CRRT initiation will be collected and used to calculate percent fluid overload using the following formula: [16, 17].

**Table 1 Tab1:** Planned data collection at time of enrollment (CRRT initiation)

Category	Data Elements
Demographics	Date of birth/Age
	Gender
	Body mass index
	Hospital admission weight
Comorbidities	Components of Charlson Index
ICU Admission Data	ICU admission date
	Admission source (hospital ward, emergency department, outside hospital transfer)
	Primary condition
	Secondary condition
CRRT Initiation Data	Clinical indication for CRRT (all that apply)
	Time from ICU admission to CRRT initiation
	Cumulative fluid balance from ICU initiation to CRRT initiation
Laboratory Data	Serum creatinine at ICU admission
	Serum creatinine at CRRT initiation
	APACHE II score at ICU admission

*CRRT* continuous renal replacement theray, *ICU* intensive care unit

%fluid overload = [(total fluid intake (L) – total fluid output (L))/ICU admission weight (kg)] x 100%. Additional patient clinical data will be updated on a daily basis to reflect clinical management, severity of illness and laboratory findings (Table 2). All laboratory values will be recorded as available, and no laboratory testing will be requested as part of CRRTnet.

**Table 2 Tab2:** Daily clinical data collection

Category	Data Elements
Severity of Illness	SOFA score components
	Need for mechanical ventilation
	Vasopressor requirements (drug and rate)
Fluid Balance	Type and volume of fluid intake
	Type and volume of recorded outputs
Nutrition	Enteral nutrition formula and volume
	Parenteral nutrition protein, calories and volume
Laboratory Data	Complete blood count: white blood cell count, hemoglobin, hematocrit, platelets
	Metabolic panel: sodium, potassium, chloride, bicarbonate, blood urea nitrogen, creatinine, phosphate, magnesium, albumin
	Coagulation parameters: INR, PTT, anti-Xa activity

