### Statistical analysis

All descriptive data will be analyzed using standard statistical methods. CRRTnet will assess for potential associations between patient characteristics, CRRT initiation and prescription parameters, and patient outcomes (mortality, length of stay, duration of AKI) using ANOVA (for normally distributed variables) or Kruskal-Wallis (for non-normally distributed variables). Multivariate proportional hazards models will be constructed, with initial inclusion of variables with <0.2 significance in univariate analyses. Additional analyses of registry data will be developed based on specific research questions.

Data analyses will be performed by Technomics Research, LLC (Minneapolis, MN) and guided by the CRRTnet registry board.

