Beyond descriptive analyses of patient characteristics and overall outcomes, we are planning on several comparative analyses. One particular area of interest is in the management of fluid overload. Our data will allow determination of fluid overload status at time of CRRT initiation, as well as daily fluid balances thereafter. While the dangers of established fluid overload have been increasing recognized in recent years, [10, 25, 26] there is a paucity of data examining different approaches to fluid management utilizing renal replacement therapy. We will examine rates of fluid removal (e.g. in ml/kg/h) and fluid overload correction to determine potential impact on patient outcomes such as renal function recovery and mortality. We hypothesize that, after adjusting for severity of illness, higher fluid removal rates will be associated with lower likelihood of renal recovery.

Another area of particular interest is anticoagulation to maintain CRRT filter patency. The KDIGO guidelines suggest regional citrate anticoagulation as the first-line method in patients without a contraindication. We anticipate that citrate anticoagulation will be associated with longer circuit life compared to heparin or no anticoagulation, a finding that has been observed in a number of clinical trials [27–30]. However, there is no consensus approach to citrate anticoagulation; while several different protocols have been published, there have been no comparative trials. Because of existing differences in citrate anticoagulation protocols among CRRTnet centers, we will be able to compare outcomes between different protocols.

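### Selecting adjustment variables by univariate p<0.2, with none exempt, does not guarantee the severity adjustment that the practice comparisons rely on

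*Protocol article*

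**What the plan says.** The protocol article, Statistical analysis, states: "Multivariate proportional hazards models will be constructed", "with initial inclusion of variables with <0.2 significance in univariate analyses". This is the only covariate rule given, and it exempts neither severity, age, comorbidity nor centre. The section then adds: "Additional analyses of registry data will be developed based on specific research questions".

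The Background gives the purpose of the comparisons: "The natural variability in practices between (and even within) centers will provide the ability to compare outcomes between different practice patterns". The Discussion names one hypothesis that depends on severity adjustment: "We hypothesize that, after adjusting for severity of illness, higher fluid removal rates will be associated with lower likelihood of renal recovery".

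Severity is well recorded. Under Data collection, Table 1 lists "APACHE II score at ICU admission", and Table 2 lists daily "SOFA score components", ventilation and vasopressors.

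**The concern.** A univariate p-value measures crude association with outcome. It does not show whether a variable confounds the practice being compared. If sicker patients are steered to a practice that helps, the harm from severity and the benefit of the practice offset each other in severity's crude association. Severity can then fail the screen in just the situation where leaving it out biases the practice effect.

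Nothing is randomised here, so the comparisons stand or fall on confounder control. Intervals computed after data-driven selection also take no account of the selection. Different models would carry different adjustment sets chosen by the data, which makes their results hard to compare.

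**Working it through.** The plan has no figure to reproduce. The Sample size section says no formal calculation was done and gives a target of 2000. The Background puts hospital mortality near 50% in ICU patients on renal replacement therapy, which suggests about 0.5 × 2000 = 1000 deaths. All effect sizes and correlations below are assumptions, because the documents give none.

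**Step 1. Severity not masked.** For a severity score standardised to SD 1 and d events, z = √d × |ln HR|. The chance of failing a two-sided p<0.2 screen is Φ(1.282 − z) − Φ(−1.282 − z). Example: d = 200, HR 1.10 gives z = 14.14 × 0.0953 = 1.348 and a chance of 0.474 − 0.004 = 47%.

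| HR per SD | 200 events | 1000 events |
|---|---|---|
| 1.05 | 70% | 39% |
| 1.10 | 47% | 4% |
| 1.20 | 10% | about 0% |
| 1.30 | 0.8% | about 0% |

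ICU deaths may be fewer than hospital deaths. At an assumed 35% there are 700; for HR 1.20, z = 26.46 × 0.182 = 4.82, and the chance of loss is still about 0%.

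**Step 2. Severity masked.** Let practice be a yes/no variable cut at the median of a normal score that has correlation ρ with severity. Severity's crude log HR is then roughly b_S + b_A × ρ × 0.399. With practice HR 0.60 (b_A = −0.511), ρ = 0.5 and b_S = 0.10, this is 0.10 − 0.511 × 0.5 × 0.399 = 0.10 − 0.102 ≈ 0. The screen then sees nothing and drops severity in about 1 − 0.2 = 80% of samples, whatever the sample size. The crude practice effect becomes b_A + b_S × 1.596ρ = −0.511 + 0.080 = −0.431, an HR of 0.65 instead of 0.60.

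**Step 3. Cox simulations** (500-600 replicates, 50% events; Monte Carlo error of a coverage near 95% is about 1 point). Coverage is for the nominal 95% interval, screened / severity forced.

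| True practice HR | Severity HR per SD | ρ | N | Dropped | Screened HR | Coverage |
|---|---|---|---|---|---|---|
| 0.70 | 1.30 | 0.5 | 2000 | 0% | 0.70 | 97% / 97% |
| 0.70 | 1.15 | 0.5 | 2000 | 21% | 0.71 | 94% / 96% |
| 0.80 | 1.10 | 0.5 | 2000 | 39% | 0.815 | 94% / 95% |
| 0.70 | 1.07 | 0.5 | 2000 | 76% | 0.73 | 89% / 96% |
| 0.60 | 1.11 | 0.5 | 2000 | 77% | 0.64 | 79% / 93% |
| 0.60 | 1.18 | 0.8 | 2000 | 82% | 0.71 | 23% / 94% |
| 0.70 | 1.15 | 0.5 | 400 | 61% | 0.72 | 93% / 94% |
| 0.60 | 1.11 | 0.5 | 400 | 79% | 0.64 | 92% / 96% |

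In the ρ = 0.8 row the mean model SE was 0.067 against an empirical SD of 0.102, so those intervals are clearly too narrow. In the row above it the figures were 0.065 and 0.075. Small comparisons lose severity more often when masking is partial, but their wider intervals hide more of the bias.

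**Step 4. Logistic simulations with masking.**
- A protective practice (for example true OR 0.50) with weak severity effects: severity dropped in 60-64% of datasets at n=500 and 17-33% at n=2000. Coverage was 86-93% screened against 95-96% forced. The true OR of 0.50 was estimated as 0.52-0.56.
- A milder link between severity and practice use: dropped in 48-58% and 8-19%, with coverage 90-94% and 91-95%.
- Severity spread over six correlated markers (severity OR 1.25, practice OR 0.55): all six were lost together in only 19-25% of datasets at n=500 and 1.5-6% at n=2000, with screened coverage of 92-94% and 90-94%.

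**The case against.** The strongest reply has three parts.

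**The plan may not contradict itself.** A reader might infer that the screen conflicts with the severity-adjusted hypothesis in the Discussion. The documents do not support that. The rule speaks of initial inclusion, and later analyses are left to be developed by research question. Renal recovery is not among the outcomes listed in parentheses in the Statistical analysis section (mortality, length of stay, duration of AKI). A general screen and a severity-adjusted analysis of one hypothesis can coexist. This part stands: the text fails to guarantee the adjustment but does not rule it out.

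**The damage depends on assumed cancellation.** This also stands. With severity OR 1.5, loss was 2% at n=500 and 0% at n=2000. With a null or harmful practice and severity OR 1.25, it was 2-12% and 0%. The registry records several severity measures, so losing one is not losing all. The 23% coverage case needs a correlation of 0.8 and near-exact cancellation, so it marks an extreme and is not an expectation.

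**An article need not list every covariate.** Agreed; the absence of a full list is no fault. The point concerns a selection rule that the article does state.

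Two side inferences should not be pressed. APACHE II dates from ICU admission, but daily SOFA components are collected, so later severity is not unmeasured. The article does not say which time points enter the models, so entry of post-initiation mediators is possible but not shown.

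**Conclusion.** The point holds in a limited form. The stated rule can remove a severity confounder that a practice comparison needs, and nothing in the article prevents it. The exposure lies in masked confounders, weak confounders and smaller comparisons such as those between citrate protocols. There the expected harm is modest bias and coverage of about 86-93% in place of 95%, with little loss under milder assumptions and much worse only under extreme ones.

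It does not follow that the main mortality model is unsound: with 700 to 1000 events, a strong and unmasked severity score is kept almost always. All bias and coverage figures rest on assumed effects. The finding that no variable is exempt rests on the text alone.

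**What to change.** For the comparative models, replace the p<0.2 screen with a compact covariate set fixed in advance on subject-matter grounds and kept regardless of p-value. Candidates already collected are age, comorbidity, severity (SOFA components and/or APACHE II), ventilation and vasopressor use, and percent fluid overload. Use values recorded at or before CRRT initiation; a daily value from the day of start may come after it.

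Size the set to each comparison. About 1000 deaths over 20 parameters is 1000/20 = 50 events per parameter, but that uses hospital mortality and the full cohort. A spline-rich set of about 29 parameters in a 500-patient comparison with 50% deaths has 250/29 ≈ 8.6. A long list in every model is therefore not free.

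Account for centre, except where the practice compared varies only by centre. The Discussion relies on citrate-protocol differences among centres, and a centre term would remove that contrast. State there that practice and centre effects cannot be separated.

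The cost is a few sentences in the analysis section, no new data, and some degrees of freedom, felt mainly in small sub-comparisons.

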## Discussion

Severe AKI remains a common complication of critically ill patients, and recent studies suggest that the incidence of dialysis-requiring AKI is increasing [18]. CRRT has emerged as the recommended dialysis modality for hemodynamically unstable patients in the ICU, and a recent study demonstrates that CRRT is the most commonly used dialysis modality in critically ill patients with AKI [19]. CRRT provides the advantages of improved solute and fluid balance control compared to patients on intermittent therapies. Yet in reality “CRRT” is an umbrella term that encompasses multiple different modalities and approaches. A high degree of variation exists in how CRRT is prescribed and delivered between (and within) medical centers, and there is currently a paucity of high-quality evidence to guide best practices. CRRTnet was developed with the goal of establishing the largest registry of CRRT patients to date, allowing for comparison of outcomes between a variety of different CRRT practices.

Ideally, each aspect of therapy would be assessed in randomized clinical trials. However, given the complexities of critically ill patients and potential difficulties with recruitment in this population, such an approach may not be feasible to assess every aspect of CRRT care. As such, observational studies remain an important tool, particularly when significant variations in practice naturally exist. As an example, CRRTnet was modeled after the Prospective Pediatric CRRT registry (ppCRRT) [20]. Over a 4 year period and including 13 centers in the United States, the ppCRRT enrolled 370 critically ill children who underwent CRRT and characterized outcomes in this previously under-described population [21]. Subsequent studies from ppCRRT explored patient outcomes related to vascular access, [22] anticoagulation, [23] and nutritional practices [24]. These studies provided important insight into CRRT practices and outcomes in children, spurred additional research, and continue to guide best practices in this population by informing the KDIGO AKI guidelines. Although there is significantly more literature regarding CRRT practices in adults, most of this literature is comprised of relatively small studies, primarily from single-centers. As such, there remains a significant need for large, multi-center studies such as CRRTnet.

Beyond descriptive analyses of patient characteristics and overall outcomes, we are planning on several comparative analyses. One particular area of interest is in the management of fluid overload. Our data will allow determination of fluid overload status at time of CRRT initiation, as well as daily fluid balances thereafter. While the dangers of established fluid overload have been increasing recognized in recent years, [10, 25, 26] there is a paucity of data examining different approaches to fluid management utilizing renal replacement therapy. We will examine rates of fluid removal (e.g. in ml/kg/h) and fluid overload correction to determine potential impact on patient outcomes such as renal function recovery and mortality. We hypothesize that, after adjusting for severity of illness, higher fluid removal rates will be associated with lower likelihood of renal recovery.

Another area of particular interest is anticoagulation to maintain CRRT filter patency. The KDIGO guidelines suggest regional citrate anticoagulation as the first-line method in patients without a contraindication. We anticipate that citrate anticoagulation will be associated with longer circuit life compared to heparin or no anticoagulation, a finding that has been observed in a number of clinical trials [27–30]. However, there is no consensus approach to citrate anticoagulation; while several different protocols have been published, there have been no comparative trials. Because of existing differences in citrate anticoagulation protocols among CRRTnet centers, we will be able to compare outcomes between different protocols.

One novel aspect of CRRTnet is the capture and analysis of machine data. These data record all machine measurements to the second, and include pressure measurements (e.g. access and return line pressures, filter pressures, transmembrane pressures), alarms and response to alarms, any changes in prescription (including blood, dialysate and replacement flow rates), interruptions, and actual delivered therapy. To our knowledge, this is a relatively untapped source of information, and one goal of CRRTnet will be to develop algorithms for processing the information downloaded from the CRRT machine memory cards. One of the challenges of CRRT is the complexity of therapy and the increased associated workload compared to intermittent therapies [31]. By utilizing the detailed treatment data, we will be able to characterize alarm frequency and provide more precise estimates on interface time required to maintain this therapy. This information may be helpful to administrators in determining nursing models and CRRT educational programs. In addition, nursing workload can be considered an important secondary outcome that may vary between and within centers depending on variations in CRRT protocol. For example, we hypothesize that regional citrate anticoagulation will be associated with less workload compared to non-citrate anticoagulation. It will also be interesting to compare associated workload between different citrate protocols, especially if circuit filter life is similar.

An important strength of our study is that we are examining everyday practices. While findings from controlled clinical trials can sometimes be difficult to duplicate in the “real world” setting, we will provide a relatively unfiltered look. This may be particularly important when examining adverse events and complications of therapy. Conversely, it is important to recognize that CRRT is performed at a relatively high frequency at each of the study sites, which facilitates development of local expertise and maintenance of competency. Whether or not similar practices will result in similar outcomes at smaller centers with lower volumes is uncertain. Nonetheless, we believe that CRRTnet will provide important outcomes benchmarks for centers performing CRRT.

Another important strength of CRRTnet is the ability, through waiver of consent, to include all eligible participants. In terms of the practicality of obtaining informed consent for an observational study in a population similar to our proposal, much can be learned from the unfortunate experience of the PICARD study investigators where patients and substitute decision makers were approached for informed consent [32]. Enrollment was poor, with only 52% of eligible patients included, greatly hindering the generalizability of the results. Patient refusal was infrequent at all sites, suggesting that patients themselves did not have concerns or objections to having their data collected when they were able to be approached directly. However, refusal by family occurred in almost one fifth of instances, and the absence of family or appropriate proxy was listed as a cause for refusing enrollment in as high as 40% at one site. Finally, many patients could not be enrolled because of death or discharge before being seen by study personnel. Thus, countless resources were spent on conducting an observational trial that missed almost half the eligible subjects, whose data very likely would have influenced the results of the study were they included. The CRRTnet database will be highly generalizable based on the inclusion of most eligible patients.

Some limitations of our study design are worth noting. First, we will truncate CRRT data at 14 days, which will limit applicability in patients on prolonged courses of CRRT. This decision was made primarily as a feasibility measure to limit the workload associated with detailed clinical data collection; importantly, preliminary data from participating centers showed that median duration of CRRT was in the range of 6–8 days, so we will still capture the full CRRT course for the majority of patients enrolled. Second, we will not be enrolling patients with AKI who only receive intermittent dialysis therapies and we recognize that there can be significant variation in which patients are chosen to undergo CRRT versus intermittent therapies. However, it is important to note that our goal is not to establish the role of CRRT in AKI management, but rather to focus on practice variation within CRRT prescription and delivery. So while we will not be able to advocate for which patients should be managed with CRRT, we hope to inform clinicians of best practices once a decision to initiate CRRT is made.

Over the past 30 years, CRRT has developed into an important tool for the management of critically ill patients with renal failure. Despite overall improvements, there remains marked variation in CRRT practices which is driven in part by lack of evidence-based guidance. The primary goal of CRRTnet is to develop a large data repository of CRRT patients with detailed information regarding specific CRRT practices which can then be compared in relation to outcomes. We anticipate that CRRTnet will provide the nephrology and critical care communities with an important resource for planning future clinical trials as well as for benchmarking clinical outcomes.

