### Design and setting

This is a prospective, multi-center observational study of critically ill adults undergoing CRRT. Initial recruitment is planned at 4 academic medical centers in North America with significant (>50 patients per year) volume CRRT use: University of Michigan Health System (Ann Arbor, MI), University of Alberta Hospital, University of Alberta (Edmonton, Alberta), University Hospital London Health Sciences Centre (London, Ontario), and University of Mississippi Medical Center (Jackson, MS).

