	Blood gas: pH, PaO2, PaCO2, lactate, ionized calcium

For up to the first 7 days of a patient’s CRRT course, data regarding CRRT prescription and delivery will be recorded twice daily (Table 3). For days 8 thru 14, CRRT data will be captured once daily. Details of the CRRT prescription will be truncated at 14 days. Each of the initial recruitment centers performs CRRT utilizing the Prismaflex™ device (Baxter International Inc.) which has a datacard to which machine treatment data are automatically saved. These data include detailed information such as pressure measurements, fluid removal, delivered CRRT effluent dose, and all alarms, interruptions and interventions. Machine treatment data files will be downloaded and analyzed for each patient. Each site will de-identify the patient file using the de-identified patient ID assigned by the registry database in place of the patient identifier. The de-identified machine data files will be uploaded by the site into the CRRTnet Registry within each patient’s record. Data is parsed by the application and stored in the database into select data fields based on dates and time points for each day the patient is on CRRT. If the data files cannot be accessed/used, the site can manually fill in the data fields for the specified time points with data collected by the medical staff.

**Table 3 Tab3:** Daily CRRT data collection

Category	Data Elements
Vascular Access	Dialysis catheter position
	Dialysis catheter type (acute or tunneled)
	Dialysis catheter manufacturer
	Dialysis catheter size
	Any need for catheter manipulation (e.g. repositioning, replacement)
CRRT Circuit	Any circuit interruptions/replacements and reasons
	Priming solution (new circuits)
CRRT-Related Anticoagulation	Anticoagulation type (heparin, citrate, none, other)
	Anticoagulation dose
	Anticoagulation metrics
CRRT Fluids	Type of solution
	Modality (dialysate, pre- and/or post-replacement) and rate
	Solution additives
CRRT Dose	Prescribed effluent dose
Machine Data Card	Delivered effluent dose
	Type, number and duration of machine alarms and interruptions
	Filter life

*CRRT* continuous renal replacement theray

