## Trial status

Recruitment is currently active at the 4 medical centers mentioned above. A fifth center is undergoing evaluation to join CRRTnet. The initial planned recruitment phase is 5 years with a target enrollment of 2000 patients.

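### The citrate-protocol comparison draws on differences between only four (possibly five) centres, so it is largely or wholly confounded with centre unless protocols also vary within a centre, and the article does not say so

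*Protocol article*

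**What the plan says.** The Discussion announces several comparative analyses in addition to the descriptive work. One concerns citrate: "Because of existing differences in citrate anticoagulation protocols among CRRTnet centers, we will be able to compare outcomes between different protocols". The paragraph on machine data adds a second outcome for the same contrast: "It will also be interesting to compare associated workload between different citrate protocols, especially if circuit filter life is similar".

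On the number of centres, Design and setting says "Initial recruitment is planned at 4 academic medical centers in North America" and lists two in the United States and two in Canada. Trial status adds "A fifth center is undergoing evaluation to join CRRTnet".

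On variation within centres, the article speaks only generally. The Background says "The natural variability in practices between (and even within) centers will provide the ability to compare outcomes between different practice patterns", and the Discussion says that "nursing workload can be considered an important secondary outcome that may vary between and within centers depending on variations in CRRT protocol". It does not say how many citrate protocols are in use, which centre uses which, whether any centre uses more than one, or whether a protocol may change during the five years of recruitment. The limitations paragraph of the Discussion covers the 14-day truncation of CRRT data and the absence of patients treated only with intermittent dialysis. It does not mention confounding of practice with centre.

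**The concern.** The sentence on citrate gives differences among centres as the reason why protocols can be compared. For a practice that varies between patients in the same hospital, a centre term removes hospital differences and leaves a usable contrast. For a practice that is fixed by hospital, the centre term removes the practice effect as well. Leaving it out credits every other difference between the hospitals to the protocol: case mix, staffing, ICU discharge policy, country. Adjustment for recorded patient characteristics reduces the case-mix part but not the rest.

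This is a matter of design, so a fuller analysis plan could not supply the missing information. It matters because the same paragraph says that citrate protocols have not been compared in trials, and the article hopes to inform best practice and to set benchmarks. A result that mainly reflects which hospital treated the patient could be read as evidence for one protocol over another.

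**Working it through.** The plan states no power, alpha or derived sample size, so there is no figure to reproduce. Two checks apply.

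**1. Can protocol be separated from centre?** Take a model with one indicator per centre, add protocol indicators, and see whether the rank of the design matrix rises. If it does not, no protocol effect is estimable after fixed centre effects.

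| Layout (4 centres) | Rank, centre only | Rank, centre + protocol | Between-centre residual df (centres − protocols) |
|---|---|---|---|
| Four protocols, one per centre | 4 | 4 | 4 − 4 = 0 |
| Two protocols, two centres each | 4 | 4 | 4 − 2 = 2 |
| One centre uses two protocols | 4 | 5 | a within-centre contrast exists |

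A fifth centre changes little: five distinct protocols again leave 0 df, and two protocols over five centres leave 5 − 2 = 3. The number of patients does not enter.

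**2. How far could a patient-level test mislead?** This is an illustration for the two-versus-two layout.

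Inputs from the article:
- 2000 patients (Sample size) over 4 centres, so 2000 / 4 = 500 per centre.
- Mortality of 50%, the level that the Background gives for hospital death in ICU patients on renal replacement therapy.

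Assumptions not in the article:
- The two-versus-two split.
- No true protocol effect.
- Intra-centre correlation (ICC) of 0.005 to 0.05.
- Either all patients on citrate (m = 500 per centre) or half (m = 250). Table 3 lists heparin, none and other beside citrate, so m = 500 is an upper bound under equal recruitment.

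Formulas:
- Design effect: DE = 1 + (m − 1) × ICC.
- True type I error of a nominal 5% test that ignores centre: 2 × [1 − Φ(1.96 / √DE)].

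Worked case, m = 500 and ICC = 0.02:
- DE = 1 + 499 × 0.02 = 10.98, and √DE = 3.31.
- 1.96 / 3.31 = 0.59, so the type I error is about 0.55.
- Naive standard error of the difference: √(0.25 × 2/1000) = 0.0224. True standard error: 0.0224 × 3.31 = 0.074.

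| ICC | DE, m = 500 | Effective N of 2000 | Type I error, m = 500 | Type I error, m = 250 |
|---|---|---|---|---|
| 0.005 | 3.5 | 572 | 0.29 | 0.19 |
| 0.01 | 6.0 | 334 | 0.42 | 0.29 |
| 0.02 | 11.0 | 182 | 0.55 | 0.42 |
| 0.05 | 26.0 | 77 | 0.70 | 0.59 |

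For m = 500, the difference detectable with 80% power appears to be (1.96 + 0.84) × 0.0224 = 0.063, about 6 percentage points, if centre is ignored. A valid centre-level test on 2 df (noncentral t) needs about 24, 31, 42 and 64 points at the four ICCs.

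**The case against.** A reader might infer that protocol and centre are one and the same variable here, and that the comparison is therefore impossible. The documents do not support that.

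- No section says that each centre runs a single citrate protocol or keeps it for five years. The Background and Discussion assert practice variation within centres, and Table 3 records anticoagulation type, dose and metrics, so within-centre differences could be analysed. One centre with two protocols is enough to make a contrast estimable. This stands, and it is why the point is conditional. But those statements concern CRRT practice in general; the one sentence that gives the source of the citrate contrast names differences among centres.
- The number of centres is not capped at four. This also stands, though a fifth barely alters the degrees of freedom.
- The article claims comparison, not causation. Statistical analysis speaks of potential associations, and the Background presents results as preliminary data for trials. So a descriptive, hypothesis-generating comparison remains available. What fails is attribution to the protocol, and the citrate sentence carries no such caveat.
- The figures rest on a layout, an outcome and ICCs that the article does not give, and they concern mortality rather than circuit life or workload. This stands: they show direction and possible scale, and do not forecast what the registry will find.
- The handling of centre may be specified in a full plan. Agreed: the absence of a centre term from this article is not part of the point.

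**Conclusion.** The point holds in conditional form. A citrate-protocol contrast drawn from differences among four or five centres is largely or wholly confounded with centre unless protocols also vary within a centre. The aliasing result needs no numerical assumption: with one protocol per centre there are 0 df, and with two protocols over two centres each there are 2 df and nothing is estimable after fixed centre effects.

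The size of the error from ignoring centre depends on the assumptions above: a true type I error of about 29% to 70% with 500 citrate patients per centre, and 19% to 59% with 250. Neither range is a property of the registry. The point deserves correction because it changes what the study can conclude about citrate protocols. It does not affect the registry's other aims or comparisons of practices that differ between patients within a centre.

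**What to change.** - In the Discussion, reword the citrate sentence and the workload comparison between citrate protocols. Say that between-centre differences will be reported descriptively, by centre, as hypothesis-generating.
- State which centres use which citrate protocol and whether any centre uses more than one or changes protocol during recruitment.
- Limit inference about a protocol effect to within-centre variation where it exists, for example a dated protocol change, adjusted for calendar time.
- If a between-centre test is shown, use centre as the unit and report its degrees of freedom.
- Add confounding of protocol with centre to the limitations in the Discussion.

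The cost is rewording and a short tabulation of protocols by centre; no new data collection on patients is needed. The downside is that one advertised comparison becomes mainly descriptive.
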